## **5.0 THERAPEUTIC/DIAGNOSTIC AGENTS**

Acupuncture treatment will be given by certified, licensed MSK staff acupuncturists. All have extensive clinical experience in treating cancer patients.

**Acupuncture Needles:** Seirin acupuncture needles will be used in this study. The needles are purchased and distributed from Seirin® in the United States (<http://www.seirinamerica.com>). Seirin acupuncture needles are approved by the FDA ([http://www.accessdata.fda.gov/cdrh\\_docs/pdf/K962809.pdf](http://www.accessdata.fda.gov/cdrh_docs/pdf/K962809.pdf)).

## **6.0 CRITERIA FOR SUBJECT ELIGIBILITY**

### **6.1 Subject Inclusion Criteria**

- English-speaking
- Age  $\geq$  18 years old
- Solid tumor survivors with no evidence of disease
- Moderate to severe CIPN, defined by symptoms such as numbness, tingling, or pain ratings of 4 or greater on a 0-10 numeric rating scale (NRS)
- Have completed neurotoxic chemotherapy at least 3 months prior to enrollment
- If taking anti-neuropathy medications, they are on a stable regimen (no change in 3 months)

### **6.2 Subject Exclusion Criteria**

- Patients with a pacemaker
- Prior acupuncture treatment within 5 years of enrollment

## **7.0 RECRUITMENT PLAN**

Our primary recruitment approach will be via sending recruitment letters to potential participants. Potential patients who meet basic eligibility criteria will be identified via querying Dateline and sent a recruitment letter. The recruitment letter will introduce the study to potential participants and state that we are conducting a study of acupuncture for neuropathy and if interested in learning more about the study, the patient should contact the research study assistant. The letter provides patients with an opt-out option if they do not wish to participate or be contacted further. We have successfully used this recruitment method for similar studies.

In addition to sending recruitment letters, potential participants also can be identified and referred to the study RSA by protocol investigators or other MSK healthcare providers or can be self-referred. The study PI and other members of the research team will reach out to colleagues about the study and present at Service meetings. Information about the protocol will also be provided in lay language on MSKCC's web site and on [clinicaltrials.gov](http://clinicaltrials.gov). Additionally, printed materials will be posted in clinic areas where we have successfully posted study materials for other Integrative Medicine studies before (e.g., MSK's solid tumor clinics, cancer survivorship clinic, and integrative

medicine clinic). Permission from the clinic sites will be obtained before posting in any location. All study recruitment materials will be submitted to, and approved by, the Institutional Review Board. We have used these recruitment strategies successfully to recruit participants to similar studies.

Integrative Medicine Research Study Assistants (RSAs) will screen potential interested and eligible patients, and schedule screening and consenting appointments. A study investigator will confirm eligibility. A study investigator or RSA specially trained for participation in the study will obtain informed consent. After establishing eligibility, the study staff will register participants.

Initial contact with prospective subjects typically will be made by a member of the study team. The recruitment process presents no more than minimal risk to patient privacy, and minimal PHI will be maintained on screening logs. For these reasons, we seek a (partial) limited waiver of authorization to: (1) review medical records to identify potential research subjects and obtain information relevant to the enrollment process; (2) converse with patients regarding possible enrollment; (3) handle PHI contained in those records and provided by potential subjects; and (4) maintain minimal PHI information in a screening log of patients approached.

## **8.0 PRETREATMENT EVALUATION**

Attendings will approve potential patients per eligibility requirements noted above. Baseline measures to assess CIPN severity will be conducted by a chemotherapy nurse, research nurse, or physician. At baseline, the following information will be collected.

- ECOG Performance Status
- Severity of CIPN as defined by NCI-CTC 4.0
- FACT-GOG/NTx questionnaire
- Neuropathy Pain Scale (NPS)
- Numeric Rating Scale (NRS)
- Treatment Expectancy Scale (TES)
- Pain medication list
- Quantitative Sensory Testing (QST)
- Controlled Pain Modulation (CPM)
- Insomnia Severity Index (ISI)
- Hospital Anxiety and Depression Scale (HADS)
- Brief Fatigue Inventory (BFI)

### **Numeric Rating Scale (NRS)**

The primary endpoint will be measured by NRS of the most bothersome CIPN symptom. The numeric rating scale is an 11-point numeric scale with 0 representing no symptoms and 10 representing the worst symptoms imaginable. The NRS has been widely used to measure severity of symptoms, especially pain. Its high reliability and validity has been observed in prior studies. In clinical trials for multiple conditions, i.e. diabetic neuropathy, chronic low back pain, a reduction of 2 points or 30% on the NRS scores has been shown to be clinically significant. The NRS is a valid and reliable scale to measure CIPN symptoms (pain, tingling, numbness) intensity. It

is simple and can be administered both verbally and in writing, and is effective as an initial screening tool to assess patient's eligibility for the trial. The components of this measurement can be found in the Appendix A. It will be collected at baseline and at weeks 4, 8, and 12 for the acupuncture group and sham acupuncture group. The usual care control group will complete the questionnaire at baseline and weeks 4, 8 and 12. It takes no more than 2 minutes to complete. Week 4 questionnaires for the usual care group may be completed over the phone.

### **NCI –CTC 4.0**

The National Cancer Institute (NCI) of the National Institutes of Health (NIH) has published standardized definitions for adverse events (AEs), known as the Common Terminology Criteria for Adverse Events (CTCAE, also called "common toxicity criteria"), to describe the severity of organ toxicity for patients receiving cancer therapy. Toxicity is graded as mild (Grade 1), moderate (Grade 2), severe (Grade 3), or life-threatening (Grade 4), with specific parameters according to the organ system involved. Death (Grade 5) is used for some of the criteria to denote a fatality. Severity of CIPN defined by NCI-CTC 4.0 is detailed in Appendix B. CIPN severity will be assessed at baseline and weeks 8 and 12. The CIPN grade for the baseline measure can be obtained from the patients EMR if it was measured within two weeks of the consent/baseline visit.

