| Study Allocation Belief                                                                                          |   |   |   | X |
| Pain Medication List                                                                                          | X | X | X | X |
| Safety Assessment                                                                                                | X | X | X |   |
| Quantitative Sensory Testing (QST)                                                                               | X |   | X | X |
| Controlled Pain Modulation (CPM)                                                                                 | X |   | X | X |

1. In the case of any missed sessions during the study, the testing, questionnaires and other assessments should occur in the same week as planned. In the case of early discontinuation of treatment, all attempts will be made to collect the questionnaires until the end of the study.
2. ECOG Performance Status will be assessed  $\leq 28$  days before the consent.
3. The medication lists will include both prescription and non-prescription pain medication.
4. Patients will be monitored for side effects at each acupuncture and sham acupuncture session .
5. This will be performed by an IMS research study assistant who will go through training before the initiation of the study. A window of + 1 week applies to the baseline assessments, and a window of +/- 3 days applies to week 8 and week 12 assessments.
6. Can be performed over the phone.

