## **12.0 CRITERIA FOR THERAPEUTIC RESPONSE/OUTCOME ASSESSMENT**

The primary endpoint will be measured by NRS of the most bothersome CIPN symptom and measured at time of consent (baseline) and at 8 weeks, after the final acupuncture session for the acupuncture or sham acupuncture arms and at baseline and after 8 weeks of usual care for patients randomized to the usual care arm. Secondary endpoints will be measured by the FACT/GOG-NTx, NPS, NCI-CTC 4.0, ISI, HADS, BFI, TES, QST, and CPM. Additionally, NRS will be assessed as a secondary aim at baseline, 4 weeks, and 12 weeks for all arms. All non-NRS secondary endpoints will be assessed at baseline, 8 weeks and 12 weeks. The NPS and FACT-GOG/NTX will also be assessed at 4 weeks.

All patients enrolled in the study who completed acupuncture or sham acupuncture will be included in the analyses, and any patients who withdraws from the study or who is lost to followup will be described.

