### **14.0 BIOSTATISTICS**

The main objective of this study is to provide preliminary data on the effect of acupuncture in reducing persistent CIPN symptoms from baseline to after 8 weeks of acupuncture or sham acupuncture as compared to a usual care control in order to design a fully powered randomized trial of acupuncture versus sham acupuncture. The enrollment goal is 75 patients.

To help plan the definitive trial, we will derive estimates for the standard deviation of all endpoints and the correlation between baseline and follow-up for each endpoint. For each of the patient reported outcomes (NPS, FACT/GOG-NTx, NRS) analysis will be by ANCOVA with the baseline score and most bothersome CIPN symptom as covariates.. Treatment will be coded as dummy variables for any treatment and real acupuncture, hence the three groups will be coded 1/1, 0/1, and 0/0 for acupuncture, Sham acupuncture, and UC respectively. Similarly, to account for type of most bothersome CIPN symptom (tingling vs numbness vs pain) dummy variables for tingling, numbness, and pain will be coded 1/0, 0/1, and 0/0, respectively. Where the week of follow-up is given in the subscript, we will calculate:  $NRS_8 = \beta_1 NRS_0 + \beta_2 \text{Real Acupuncture} + \beta_3 \text{Any Acupuncture} + \beta_4 \text{Tingling} + \beta_5 \text{Numbness} + c$ . The primary endpoint will be NRS of the most bothersome CIPN symptom at 8 weeks.

We will estimate the change in the proportion of patients with a CIPN severity of grade 3 or higher according to the NCI-CTC 4.0 from baseline to 8 and 12 weeks along with an exact 95% confidence interval, separately. To explore the relationship between quantitative sensory testing (QST) and

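### The baseline NCI-CTC grade alone may come from the medical record, with no requirement that the entry precede randomization, so a change of source, rater or timing may pass for, or mask, a change in CIPN grade

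*Protocol*

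**What the plan says.** Only the protocol was available for this point. Five places in it matter.

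- **Schedule (Section 8.0, NCI-CTC 4.0).** "CIPN severity will be assessed at baseline and weeks 8 and 12". The same paragraph then adds, for the first time point only: "The CIPN grade for the baseline measure can be obtained from the patients EMR if it was measured within two weeks of the consent/baseline visit". It gives no such option for weeks 8 and 12.
- **Who grades (opening of Section 8.0).** "Baseline measures to assess CIPN severity will be conducted by a chemotherapy nurse, research nurse, or physician". No section names the grader at weeks 8 and 12 or asks for the same grader throughout.
- **Mode (Table 2, footnote 6).** "Can be performed over the phone". The footnote is attached to the whole NCI-CTC row, baseline included.
- **Analysis (Section 14.0).** "We will estimate the change in the proportion of patients with a CIPN severity of grade 3 or higher", from baseline to 8 and to 12 weeks, with an exact 95% confidence interval. The ANCOVA with treatment terms is specified for the patient-reported outcomes. No comparison between arms is stated for the grade.
- **Status (Section 12.0).** "Secondary endpoints will be measured by the FACT/GOG-NTx, NPS, NCI-CTC 4.0, ISI, HADS, BFI, TES, QST, and CPM". The grade is therefore a secondary endpoint. Section 14.0 fixes the primary one: "The primary endpoint will be NRS of the most bothersome CIPN symptom at 8 weeks".

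**The concern.** A change score is interpretable only if both ends are measured in the same way. Here the baseline end may be a routine chart entry, while the follow-up ends have no such option. The summary is a before-and-after difference in a proportion, so any systematic difference between charted grades and later grades enters the estimate in full. The exact interval covers sampling error only.

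Timing is a second problem. The two-week window is tied to the consent/baseline visit without saying on which side of it the entry must fall. Table 2 is stricter for ECOG status, which footnote 2 requires before consent. Read literally, a grade charted after randomization, and after treatment started, would qualify as baseline. In the treated arms it could then carry some early treatment effect and hide part of a real change.

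The protocol guards against rater differences elsewhere: for quantitative sensory testing, Section 8.0 asks that one assistant do a participant's measurements before and after treatment where possible. The clinician-judged grade has no comparable rule.

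**Working it through.** The protocol gives no expected rate, precision or power for the NCI-CTC grade, so there is no stated figure to reproduce. The arithmetic below only illustrates scale.

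**Inputs from the protocol:** 75 patients, 25 per arm; endpoint is the change in the proportion at grade 3 or higher.

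**Assumed inputs (none is in the protocol):**
- p, the true proportion at grade 3 or higher: 0.10 to 0.40, the same at both times (no true change).
- f, the share of baseline grades taken from the record: 0.25 to 1.
- se and sp, the sensitivity and specificity of the record grade against the grade that would be given at follow-up.

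**Formula.** The expected apparent baseline proportion is (1 - f)p + f[se·p + (1 - sp)(1 - p)]. Subtracting it from p gives

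apparent change = f × [p(1 - se) - (1 - sp)(1 - p)].

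The sign depends on whether the severe cases missed by the record, p(1 - se), outnumber the false ones it adds, (1 - sp)(1 - p).

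**Example.** With p = 0.20, f = 0.5, se = 0.5 and sp = 1.0: 0.5 × [0.20 × 0.5 - 0 × 0.80] = 0.05, an apparent rise of 5 points. With se = 0.9 and sp = 0.85 instead: 0.5 × [0.20 × 0.1 - 0.15 × 0.80] = 0.5 × (0.02 - 0.12) = -0.05, an apparent fall of 5 points.

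**Results with all baselines from the record (f = 1), in percentage points:**

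| Record grade (se / sp) | p = 0.10 | p = 0.20 | p = 0.30 | p = 0.40 |
|---|---|---|---|---|
| Misses half of severe cases (0.5 / 1.0) | +5.0 | +10.0 | +15.0 | +20.0 |
| Intermediate (0.7 / 0.95) | -1.5 | +2.0 | +5.5 | +9.0 |
| Good agreement (0.9 / 0.95) | -3.5 | -2.0 | -0.5 | +1.0 |
| Over-grades (0.9 / 0.85) | -12.5 | -10.0 | -7.5 | -5.0 |

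The shift is proportional to f: at f = 0.5 every entry halves, and at f = 0.25 it is a quarter. Over f = 0.25 to 1, under-charting gives a rise of about 1 to 20 points and over-grading a fall of about 1 to 13.

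**Scale.** Section 14.0 does not say clearly whether the change is summarised by arm or pooled. The exact 95% interval for a single proportion of 20% is 7% to 41% for 5 of 25, and 12% to 31% for 15 of 75. These are not intervals for the change, but they show how coarse the endpoint is.

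**Timing.** This step needs no agreement figures. Section 4.2 gives two sessions a week for the first two weeks, so 2 × 2 = 4 of the 10 sessions could fall within two weeks of the visit if treatment starts promptly. The interval between the baseline visit and the first session is not stated, so four is an upper figure.

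**The case against.** The strongest case is that little of this need happen.

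- **Record use is optional.** The charted grade may come from the same clinician who grades later. Section 8.0 gives baseline grading to nurses or physicians, and a chart entry is not shown to come from anyone else. This stands: a reader might infer that a rater change will be counted as a change in neuropathy, but the text supports only that it may be.
- **The follow-up grader is not named.** That weeks 8 and 12 are graded specifically for the study is an inference from the missing record option. Because Section 8.0 allows three roles, raters can also differ without any record use. Both remarks are correct. They do not remove the difference in permitted source.
- **Telephone grading.** A reader might see this as a further contrast between baseline and follow-up. It is not, because footnote 6 covers the whole row.
- **Direction.** Assuming that charts always under-record severe neuropathy produces only apparent rises. Nothing in the protocol supports that assumption, and the table shows falls and near-zero shifts as well.
- **Extent.** Recruitment is mainly by letter to disease-free survivors at least three months past chemotherapy (Sections 6.1 and 7.0). Nothing suggests that most will have a grade charted within two weeks, so f near 1 is an extreme case.
- **Timing.** The sentence sits in the pretreatment section and is most naturally read as meaning a recent existing grade. That is probably the intent, but the wording does not require it.
- **Randomized contrasts.** For entries made before randomization, the source is not tied to arm, so its expected effect on a difference between arms is about zero. This is correct, but Section 14.0 states no such contrast for this endpoint. Nor does the argument cover entries made after treatment began.

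**Conclusion.** The point holds in a limited form. The protocol permits a different source for the baseline grade than for the later grades, leaves the date of a record entry open on the far side of randomization, and analyses the result as an uncontrolled pre-post change. A shift in source, rater or timing may therefore be read as a change in CIPN, or conceal one, outside the reported confidence interval.

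Its direction and size cannot be determined from the protocol. The ranges shown rest wholly on assumed prevalence, agreement and share of record grades. The largest values need every baseline to come from a poorly agreeing record; with good agreement the shift is small.

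The reach is one secondary endpoint of a pilot trial. The primary analysis of the patient-reported NRS is untouched. The change is worth making because it is cheap.

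**What to change.** In the NCI-CTC 4.0 paragraph of Section 8.0, delete the sentence that allows the record grade. State that the nurse or physician already named in that section grades NCI-CTC at the baseline visit, before randomization, and that the same type of grader does so at weeks 8 and 12.

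If the record option is kept, the minimum is to accept an entry only when it was made before randomization, and to record for each patient whether the baseline grade came from the record or from the visit.

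The cost is one edited sentence and, for a patient recently graded in clinic, a few minutes of duplicate grading at a visit that already takes place for sensory and pain-modulation testing. Sample size and treatment do not change. Grading need not be restricted to in-person assessment.

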### **FACT/GOG-Ntx**

The FACT/GOG-Ntx questionnaire is comprised of the FACT-G plus the 11-item Ntx subscale. Only the 11 items from the Ntx subscale of the FACT/GOG-Ntx questionnaire will be administered in this study. The 11-item neurotoxicity subscale covering sensory neuropathy, motor neuropathy, hearing neuropathy, and dysfunction associated with neuropathy to assess the details of neurotoxicity symptoms in the patient. It correlates with meaningful clinical changes in neuropathy and takes about 2 minutes to finish. The FACT/GOG-Ntx has demonstrated reliability and validity, with a Cronbach's alpha of 0.81 for the neurotoxicity subscale and an overall Cronbach's alpha of 0.84. Further, the FACT/GOG-Ntx has demonstrated sensitivity to meaningful clinical distinctions and change over time. Higher scores on the Ntx subscale of the FACT/GOG-Ntx represents higher functioning and fewer/less severe CIPN symptoms. The FACT/GOG-Ntx has been validated for self, interviewer, and computer administration. Appendix A lists the components of this measurement. It will be collected at baseline and at weeks 4, 8, and 12 for the acupuncture group and sham acupuncture group. The usual care control group also will complete the questionnaire at baseline, week 4, weeks 8 and 12. Week 4 questionnaires for the usual care group may be completed over the phone.

### **Neuropathic Pain Scale (NPS)**

The Neuropathic Pain Scale (NPS) is a multidimensional tool that uses self-report visual analogue scales (VAS) to quantify, on a scale of 0-10, global pain intensity and unpleasantness and eight other descriptive qualities of neuropathic pain. The NPS also includes one semi-structured question about temporal sequence. It takes no more than 2 minutes to complete. Each of the individual items in the NPS serves as a stand alone score. All 10 of the items are relevant to the goals of the study and will be summed up to produce a total score. The NPS is capable of distinguishing neuropathic pain from non-neuropathic pain. The 10 items demonstrate weak correlations with one another, supporting their discriminate validity. Appendix A lists the components of this

measurement. It will be collected at baseline and at weeks 4, 8, and 12 for the acupuncture group and sham acupuncture group. The usual care control group will complete the questionnaire at baseline and weeks 4, 8 and 12. It takes no more than 2 minutes to complete. Week 4 questionnaires for the usual care group may be completed over the phone.

### **Treatment Expectancy Scale (TES)**

Pre-randomization treatment expectancy will be assessed using a validated measure. The Treatment Expectancy Scale (TES) is a 4-item instrument developed by [name] (co-PI) et al. TES is scored by adding up the score of each 4 items, with 1 indicating “Not at all agree” and 5 indicating “Completely agree” with the expected improvement as result of acupuncture. The score of instrument ranged from 4 to 20 out of a possible 4 to 20, with higher scores indicating greater expectancy. Outcome expectancy has long been considered an important predictor of treatment outcomes and has gained important consideration in acupuncture in recent years. It has demonstrated reliability (Cronbach’s  $\alpha$  of 0.82) and validity and is positively correlated with patient self-reported efficacy and satisfaction. The TES has also been validated in breast cancer survivors and is sensitive to change over time in response to acupuncture treatment. In our previous study, we found expectancy was stable overtime in the waitlist control group. Baseline expectancy predicted treatment outcomes of acupuncture. The TES will also be administered at weeks 4, 8, and 12. (Appendix A)

### **Pain Medication List**

The pain medication list will be collected at baseline, and weeks 4, 8, and 12. The information can be captured via a phone call for the usual care group at week 4. The form lists the name and dosage of the neuropathy medication the patient is taking, if any. The lists will be compared before and at week 8 to determine if the medication was dose reduced or escalated. If the dosage or frequency resulted in total daily dosage increases, then it will be considered dose escalation. If the total daily dosage decreases, then it will be considered dose reduction. (Appendix D)

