| Primary Objective                                  | To obtain preliminary data on the effects of acupuncture and sham acupuncture compared to usual care in reducing chemotherapy-induced peripheral neuropathy (CIPN) severity to help design a fully powered randomized trial.                                                                                                                                                                                                                                                                                                                                                                                                                                        |
| Secondary Objectives                               | 
To obtain estimates of the change in CIPN severity
 
To elucidate the mechanisms of acupuncture by obtaining estimates of tactile threshold, vibration threshold, thermal threshold and controlled pain modulation.
 
To obtain estimates of the change in insomnia, anxiety, depression, and fatigue symptoms.
 
To obtain estimates of the correlation of treatment expectancy and treatment response among patients who undergo acupuncture or sham acupuncture.
 
To estimate the proportion of patients with a dose reduction and the proportion with a dose escalation of neuropathy medication during the course of the 12 weeks.
 |
| Patient Population                                 | Solid tumor cancer survivors on no or stable neuropathy medication with persistent moderate to severe CIPN, defined as numbness, tingling, or pain ratings of $\geq 4$ on the numeric rating scale (NRS), at least 3 months after neurotoxic chemotherapy completion.                                                                                                                                                                                                                                                                                                                                                                                               |

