**Secondary Objectives:**

- To obtain estimates of the change in chemotherapy-induced peripheral neuropathy (CIPN) severity
- To elucidate the mechanisms of acupuncture by obtaining estimates of tactile threshold, vibration threshold, thermal threshold and controlled pain modulation. To obtain estimates of the change in insomnia, anxiety and depression, and fatigue symptoms.
- To obtain estimates of the correlation of treatment expectancy and treatment response among patients who undergo acupuncture or sham acupuncture.
- To estimate the proportion of patients with a dose reduction and the proportion with a dose escalation of neuropathy medication during the course of the 12 weeks.

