### **4.2 Intervention**

Subjects will be stratified based on the type of the most bothersome CIPN symptom (tingling vs numbness vs pain) and severity of such symptom (moderate 4-6 vs 7-10 on NRS) first. They will then be randomized at a 1:1:1 ratio to the acupuncture group (ACU), sham acupuncture group (SHAM) or usual care group (UC). Integrative Medicine Service acupuncturists will perform the acupuncture

and sham acupuncture treatments. The acupuncture group and sham acupuncture group will undergo 8 weeks of outpatient acupuncture or sham acupuncture treatments (twice weekly for 2 weeks, then weekly for 6 weeks, 10 treatments in total). We have designed this approach to standardize acupuncture treatment for future broad use; it is based on the understanding that CIPN is a global symptom complex rather than individual isolated or local symptoms. We will encourage all patients to keep their pain medication regimen unchanged during the 8-week intervention and will record all pain medication usage during the study. A window of  $\pm 3$  days applies to acupuncture sessions. A missed session will not be made up without prior approval from the PI. Highly experienced and licensed acupuncturists who are part of MSK's Integrative Medicine Service will perform the acupuncture or sham acupuncture treatments.

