neuropathy we will use linear regression to assess the association between NRS and TT, VT, and THT at baseline, and the association between change in NRS with change in TT, VT, and THT. For the mechanistic studies, we will use an interaction term between baseline CPM and real acupuncture to predict NRS at 8 weeks:  $NRS_8 = \beta_1 NRS_0 + \beta_2 CPM_0 + \beta_3 \text{Real Acupuncture} + \beta_4 CPM_0 \times \text{Real Acupuncture} + c$ . We will also test acupuncture-induced changes in CPM as  $CPM_8 = \beta_1 CPM_0 + \beta_2 \text{Real Acupuncture} + \beta_3 \text{Any Acupuncture} + c$ . We will also explore the relationship between treatment expectancy and response adjusting for baseline CIPN and treatment arm using multivariable linear regression comparing acupuncture versus sham acupuncture:  $NRS_8 = \beta_1 NRS_0 + \beta_2 \text{Real Acupuncture} + \beta_3 \text{Treatment Expectancy} + c$ . We will also estimate the change in mean HADS, BFI and ISI scores from baseline to 8 and 12 weeks along with a 95% confidence intervals, separately. We will also estimate the proportion of patients with a dose reduction and the proportion of patients who experience a dose escalation of neuropathy medication during the course of the 12 weeks along with an upper 90% confidence interval. All analyses will be by intent to treat, with participants analyzed according to allocation irrespective of treatment actually received. We will use multiple imputation, including 4 week outcome, for missing data at 8 weeks. Patients with 4 and 8 week outcomes are missing, they will not be included in the analysis.

For a trial with 25 patients per group, and an anticipated correlation between baseline and follow-up measures of 0.5, we will be able to calculate the upper bound of a one-sided, 90% confidence interval for the coefficients of any treatment and real acupuncture to approximately 0.35 standard deviations.

Last year, 935 solid tumor survivors had a diagnosis of persistent CIPN 3 months after chemotherapy completion. A recent study showed that among breast cancer survivors 28% reported moderate to severe CIPN 3 months after chemotherapy completion. Therefore, we anticipate 262 patients are eligible per year for our proposed study. Assuming at least a 15% enrollment rate of the eligible patients the estimated accrual is 3-4 patients per month, the estimated accrual period is between 19 and 25 months in order to identify 75 eligible patients.

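### Medication dose change is classified from baseline and week 8 only, although the secondary objective and Section 14.0 estimate it over 12 weeks

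*Protocol*

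**What the plan says.** The protocol describes the same quantity in three places.

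- **Objective.** Table 1 in Section 1.0 and the secondary objectives in Section 2.0 call for the proportions with a dose reduction and with a "dose escalation of neuropathy medication during the course of the 12 weeks".
- **Analysis.** Section 14.0 begins "We will also estimate the proportion of patients with a dose reduction" and continues with those who "experience a dose escalation of neuropathy medication during the course of the 12 weeks", to be reported with an upper 90% confidence interval.
- **Derivation.** Section 8.0, under Pain Medication List, gives the rule that turns the lists into an outcome: "The lists will be compared before and at week 8 to determine if the medication was dose reduced or escalated". A higher total daily dosage counts as escalation and a lower one as reduction.

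The same part of Section 8.0 sets the collection times: "The pain medication list will be collected at baseline, and weeks 4, 8, and 12". The study calendar (Table 2) and Section 10.0 give the same four times.

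Two other statements bear on the point. Section 4.2 says "We will encourage all patients to keep their pain medication regimen unchanged during the 8-week intervention". Table 1 describes the population as "Solid tumor cancer survivors on no or stable neuropathy medication", so patients who take no such medication may enrol.

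**The concern.** The objective and the analysis cover 12 weeks, while the classification rule covers 8. No other part of the protocol extends the rule to week 12, so the outcome as derived is not the outcome named in the objective. Two analysts working from the same data, one following Section 8.0 and the other Section 14.0, could report different proportions.

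The missing weeks are not interchangeable with the others. The request to keep the regimen unchanged applies to the 8-week intervention. The rule therefore looks only at the period in which change is discouraged and omits the four weeks to which that request does not extend. A figure derived this way but labelled as a 12-week proportion could make medication use look more stable than it was. The pilot's estimates are meant to inform the design of a later trial, so the label should match the derivation.

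**Working it through.** **Is there a figure to reproduce?** No. The protocol states no expected proportion, precision or sample size for medication change. The check is therefore a comparison of the text, followed by an illustration that rests on assumed rates.

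**Step 1. The passages side by side.**

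| Place in protocol | What it fixes | Window |
|---|---|---|
| Section 1.0 (Table 1) and Section 2.0 | Secondary objective | 12 weeks |
| Section 14.0 | Estimated proportions | 12 weeks |
| Section 8.0, Pain Medication List | Classification rule | Baseline against week 8 |
| Table 2, Section 8.0, Section 10.0 | Lists collected | Baseline, weeks 4, 8, 12 |
| Section 4.2 | Request for an unchanged regimen | 8-week intervention |

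The first two rows and the third cannot all govern the same endpoint. The fourth row shows that the data for a 12-week derivation will exist.

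**Step 2. What the rule cannot see.** A change first made between weeks 8 and 12 is not counted. A change made and reversed before week 8 is not counted either, because the week 4 list is not used. Both would be changes within the 12 weeks.

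**Step 3. Illustrative size.** Let p12 be the true proportion of patients with a change of a given type at some time in the 12 weeks. Let s be the share of those patients whose change is first made after week 8. If every earlier change is still visible at week 8, the rule yields

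p8 = p12 × (1 − s).

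Neither p12 nor s is in the protocol; both are assumed here.

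| Assumed p12 | s = 0 | s = 10% | s = one third | s = one half |
|---|---|---|---|---|
| 10% | 10% | 9% | 6.7% | 5% |
| 20% | 20% | 18% | 13.3% | 10% |
| 30% | 30% | 27% | 20% | 15% |

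For example, 20% × (1 − 1/3) = 13.3%. The row for s = one third is not a prediction: four of the twelve weeks is a third of the time, which need not be a third of the changes.

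**Step 4. Direction.** If the endpoint means any change during the 12 weeks, which is the natural sense of the objective, the week 8 rule can only miss changes, so any error is downward. If it were meant as a net comparison of baseline with week 12, a change present at week 8 and reversed by week 12 would push the other way. The protocol does not describe such a net week 12 comparison.

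**The case against.** The strongest reply is that a net comparison of baseline with the end of treatment is a legitimate definition, that the mismatch is one of wording, and that no data are lost because the week 12 list is collected anyway. It can be added that the protocol gives no rate of change after week 8, so the two windows might yield the same figure. Most of this stands. It limits the consequence, but it does not reconcile the documents: a baseline-to-week-8 comparison is legitimate only if it is labelled as one, and the objective and Section 14.0 label it as 12 weeks. A statistical analysis plan can fill in what a protocol leaves open, but here the protocol itself states two different windows.

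A reader might infer three stronger points that the documents do not support.

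- **That the reported proportions will be wrong.** They differ from the 12-week figures only if some patient's classification depends on weeks 8 to 12, or on a change reversed before week 8. With s = 0 in the illustration there is no difference.
- **That weeks 8 to 12 are when change is most likely.** Section 4.2 only encourages stability during the intervention. Nothing says what patients are told afterwards, or that changes cluster then. Such changes are plausible, no more.
- **That non-users dilute the reduction proportion.** Patients on no neuropathy medication are eligible and cannot reduce a dose, and Section 14.0 speaks of the proportion of patients under intent to treat. Yet no passage says whether they are in this denominator. Intent to treat settles analysis by allocation, not the denominator of a descriptive proportion, and that choice may properly sit in an analysis plan not shown here. The choice would affect the number: with 75 patients, an assumed 38 users and 8 reductions, it is 8/75 = 10.7% or 8/38 = 21.1%. But an all-patient proportion is a valid descriptive figure, so this is not an error in the plan.

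**Conclusion.** The inconsistency is real: the classification rule in Section 8.0 ends at week 8, while the secondary objective and Section 14.0 run to week 12. Followed as written, the rule does not deliver the stated objective, and the 12-week proportions may be understated.

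The size cannot be computed from the protocol. Under the assumptions above, a true 20% would read as somewhere between 10% and 20% as the share of changes first made after week 8 runs from one half down to none. That range depends entirely on the assumed shares and on earlier changes persisting to week 8.

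The severity is minor. This is a secondary, descriptive estimate; the week 8 NRS endpoint, its ANCOVA and the enrolment goal of 75 do not depend on it.

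**What to change.** Amend the rule under Pain Medication List in Section 8.0 so that dose reduction and escalation are classified by comparing the baseline list with those at weeks 4, 8 and 12. It will then match the 12-week window in Sections 1.0, 2.0 and 14.0. If the comparison at the end of treatment is of interest in its own right, keep it as a separate result labelled as baseline to week 8.

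As an optional clarification, the reduction proportion can also be shown among patients taking neuropathy medication at baseline, with the denominator stated.

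The cost is a few lines of text. All the lists are already scheduled, so no visit, form or patient is added, and nothing changes in how patients are managed.
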